### The intervention

The overarching project ‘VOLITION’ follows the Intervention Mapping framework ([3]) as a means of systematically applying existing literature and relevant theory to each step of intervention development and evaluation. Social and behavioural science theory was used to describe factors affecting older patients’ involvement in decision-making about their healthcare, as well as methods for improvement. Evidence from a systematic review [8], from patient, public and expert opinion and from a focus group study with older patients with multimorbidity and with GPs, enabled the refinement of logic models underpinning this work. The Intervention Mapping process will be published separately.

There are two core intervention components (see Table 2 and Fig. 2 for detail):
A patient tool to facilitate patients to convey their preferences for involvement to the GPA workshop for GPs to train them in shared decision-making orientated communication skills, delivered in the context of the challenges currently facing GPs when consulting with this patient group

**Table 2 Tab2:** The VOLITION intervention applications

Patient support tool^a^	GP workshop
**Central image**	**Delivery and facilitation by a GP**
Illustrates the spectrum of patient preferences for involvement and poses the question “where do you see yourself?”	For the purposes of role-modelling as a means of knowledge transfer
**Phrases to use during the consultation**	**Information provision**
Aimed at facilitating patients to ask for or decline participation in decision-making, accompany the central image.	GP-facilitator provides information regarding the elements of a shared decision-making approach to the consultation, in the context of older patients with multimorbidity.
Phrases are matched to the spectrum of patient preferences for involvement.	GP-facilitator delivers new messages about the potential benefits of shared decision-making. GP-facilitator uses a set of one or more meaningful premises and a conclusion to deliver these messages.
**Messages**	
Inform the patient of their right to ask for involvement in decision-making about their care.	GP-facilitator provides positive messages regarding the role of the patient and their preferences within shared decision-making. (This information is designed using evidence from the literature regarding GPs current beliefs around shared decision-making with this patient group.)
Suggest that the patient possesses the capability to state their preferences for involvement to the GP.	GP facilitator provides information about the importance and relevance of a patient-centred approach to the consultation.
Emphasise the benefits of shared decision-making for the patient.	Messages delivered by GP-facilitator suggest that the GP possesses the capability to use a shared decision-making approach to the consultation.
	GPs are asked to relay GP-facilitator’s messages to each other, and facilitator clarifies any confusion that appears during this process.
	**Role-play**
	GPs are first shown an example video-recorded consultation between the GP-facilitator (peer-model) and an actor-patient. GP-facilitator discusses the challenges of facilitating shared decision-making with the patient and how (s)he overcame them.
	GPs take turns as the GP, the patient and the observer to role-play clinical scenarios in threes.
	Individual GPs rehearse and repeat a shared decision-making approach to a role-play consultation, using a new ‘VOLITION’ model, incorporating a patient-centred, holistic approach.
	The role-play ‘patient’ states their preference for involvement in decision-making about their healthcare; their ideas, concerns and expectations; and their preferred data format for decision-related information. In this way the ‘patient’ prompts the GP to use appropriate communication skills to match their shared decision-making preferences.
	Clinical scenarios provide increasingly challenging tasks during role-play, with feedback from peers serving as an indicator of capability to the GP GP-facilitator encourages elaboration to augment the information provided in the crib sheet for the case scenario.
	**Reflective discussion in threes followed by group feedback**
	Discussion of GP’s appropriate response to patient preferences, fundamental priorities and requirements
	Discuss the experience and provide feedback to others.
	GP-facilitator encourages elaboration to augment the information provided in the crib sheet for the case scenario.
	**Supporting reference materials**
	Handbook containing the VOLITION model and all of the key messages delivered by the GP-facilitator during the workshop, the case scenarios for role-play and space for the individual to write reflective notes. Also available online.
	Online link to the video-recorded consultation between GP-facilitator and actor-patient.
	**Patient dialogue during index consultation**
	Patient provides a nudge to the GP in the form of a phrase from the patient support tool, informing the GP of their preferences for involvement in decision making about their care.
	Acts as a cue to the GP to adapt their communication skills accordingly.

^a^The support tool will also be displayed as a poster in the waiting room to prompt recall, as well as being available in leaflet form.

**Fig. 2 Fig2:**
[figure not shown]
The VOLITION intervention

The patient tool will be mailed to eligible patients ahead of their index consultation. GPs will attend the training workshop no earlier than two weeks in advance of the index consultations with participating patients. Patients in the usual care group will receive standard care.

### Data collection

#### Practice and participant descriptive data

Practice level data (list size, location and deprivation, practice size, staffing, rural/urban) and GP participant data (age, gender, ethnicity and time since qualification) will be collected at the time of recruitment. Patient demographics (age, gender and ethnicity) and health status data will be collected via self-report using pre-consultation questionnaires.

#### Collecting outcome measure data

The General Practice Patient Survey (GPPS) uses five-point Likert scales [10]. A subset of these are appropriate for evaluation of Patient Reported Outcome Measures (PROMs) [13] on the pre-consultation patient questionnaires. These questionnaires will also be used to collect patients’ pre-consultation preferences for involvement in decision-making.

A post-consultation patient questionnaire will be used to collect post-consultation PROMs. Data will include the extent to which patients felt engaged in decision-making [2], their satisfaction with care and patient empowerment [27]. A post-consultation questionnaire for GPs will collect GPs’ ratings of the extent to which they felt they involved the patient in decision-making.

Video-recordings will enable the shared decision-making process to be assessed from an observer perspective using the OPTION(5) scale (Elwyn 2014). Two researchers will independently score each clinical decision made out of 100, with higher scores indicating better shared decision-making.

Case note review by two independent researchers will take place 12 weeks after the index consultation (to ensure time for documentation of the required outcomes). Information collected will include re-attendance within 28 days and referral for investigation or to secondary care.

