**Clinical outcomes**					
Putative primary outcome					
Ratings of shared decision-making during the consultation from an observer perspective.	During data analysis	Assessment of video’d consultations by two trained researchers using the OPTION(5) score ([18] [19];)	18 GPs, 180 patients (9 GPs and 90 patients per arm)	Continuous (OPTION score 0-100%)	Mean and standard deviation, to report data descriptively. Linear hierarchical modelling to estimate between group differences* (random effect on cluster, adjustment for practice location).
Additional outcomes					
Patient-reported rating of involvement in decision-making about their healthcare	Immediately following the index consultation	Patient post-consultation questionnaire—using collaboRATE score ([18] [19];)	180 patients (90 per arm)	Continuous (collaboRATE score 0–100%)	Mean and standard deviation, to report data descriptively. Linear hierarchical modelling to estimate between group differences^a^ (random effect on cluster, adjustment for practice location). Patient and GP scores compared using logistic regression modelling (patient scores as outcome, GP scores as explanatory variable).
Patient-reported rating of feeling satisfied with the healthcare received	Immediately following the index consultation	Patient post-consultation questionnaire	180 patients (90 per arm)	Categorical, ordinal (3 point Likert scale)	Frequencies, to report data descriptively. Logistic hierarchical modelling to estimate between group differences^a^ (random effect on cluster, adjustment for practice location).
Patient-reported rating of having trust in the GP they saw				Categorical, ordinal (3 point Likert scale)	Frequencies, to report data descriptively. Logistic hierarchical modelling to estimate between group differences^a^ (random effect on cluster, adjustment for practice location).
Patient-reported rating of enablement				Discrete (PEI score 0–12)	Frequencies, to report data descriptively. Logistic hierarchical modelling to estimate between group differences^a^ (random effect on cluster, adjustment for practice location).

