Participant experiences of the intervention, participants experiences of the study	Following receipt of participant post-consultation questionnaires and consent forms	Interviews with the participants from practices assigned to the intervention	9 GPs, 15 patients	Audio-recordings for qualitative analysis	Both deductive and inductive approaches to thematic analysis

^a^Between group differences will be reported using the appropriate outcome metric with 95% confidence intervals; no p-values will be reported in this feasibility study

Using an ‘intention to treat’ approach, participants will be analysed according to their randomised allocation irrespective of intervention actually received. However, all participants will be considered adherent by definition of the protocol. There is no mechanism by which participants in the control group could receive the intervention.

An intra-cluster correlation coefficient (ICC) will be calculated within each arm (intervention and control) for academic purposes; however, this will not be used to calculate a sample size for the future definitive trial; an estimated ICC, calculated from a large relevant routine dataset, will instead be sought [40].

The appropriateness of the outcome measures for use in a future, definitive trial of the intervention will be evaluated. The consistency with which certain outcome measures (e.g. OPTION(5), CollaboRATE, and those items taken from the GPPS survey) perform with the study population, when compared with previous performance in existing literature, will be reviewed. Findings will also be considered in the context of the internal consistency of performance of these measures within the participant sample. Consideration will be given as to whether the outcome measures chosen are sensitive to the effects of the intervention in the context of older people with multimorbidity in primary care, or whether there is a need for development of new measures.

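### The involvement scores run one way, no listed outcome measures match to patient preference, and adjusting for preference cannot show whether preference changes the effect

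*Protocol article*

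**What the plan says.** **Outcome.** Table 4 of the protocol article names the putative primary outcome as "Ratings of shared decision-making during the consultation from an observer perspective", measured by OPTION(5) as a continuous 0 to 100% score and compared between arms by a linear hierarchical model. Under Collecting outcome measure data: "Two researchers will independently score each clinical decision made out of 100, with higher scores indicating better shared decision-making". Patient and GP collaboRATE scores, also 0 to 100%, rate the degree of involvement.

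**Intervention.** Table 2 describes the patient tool's phrases as "Aimed at facilitating patients to ask for or decline participation in decision-making, accompany the central image", and adds: "Phrases are matched to the spectrum of patient preferences for involvement". In the GP role-play, the person playing the patient states a preference and so "prompts the GP to use appropriate communication skills to match their shared decision-making preferences". In the index consultation, the real patient's phrase "Acts as a cue to the GP to adapt their communication skills accordingly".

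**Preference.** It is collected before the consultation on a 6-point scale and listed in Table 4 as a baseline variable. Under Preliminary evaluation of participant responses to the intervention, a secondary analysis adjusts for it, in order to indicate whether existing preferences alter the intervention's effect.

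**Use of the results.** Under Evaluation of outcome measures: "Consideration will be given as to whether the outcome measures chosen are sensitive to the effects of the intervention".

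**The concern.** The intervention can do its job in two ways: more involvement for a patient who wants it, and a respected request for less from a patient who does not. The involvement scores are set up to register the first. Nothing in Table 4 is set up to register the second as such, because no outcome compares what the patient wanted with what the patient experienced.

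The trial is meant to judge whether its measures respond to the intervention and to inform the choice of primary outcome for the definitive trial. If the arm difference in OPTION(5) is small, the planned data cannot easily separate three explanations: a weak intervention, an insensitive measure, and an average over patients in whom the intended change differs. The preference-adjusted analysis is the one place where these might be separated, and as described it cannot do so.

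**Working it through.** **The plan's own figures.** These are counts, not a power calculation: 6 practices × 3 GPs × 10 patients = 180; the minimum is 6 × 2 × 10 = 120; 180 / 2 = 90 per arm. All reproduce. The point does not depend on them, except for stratum sizes (last step).

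**Inputs for the illustration.** The protocol gives no preference distribution, no effect size and no OPTION(5) items, so all three inputs are assumptions:
- *q*: share of patients who prefer to decline involvement
- *d*: gain in OPTION(5) among patients who want involvement, set to 10 points
- *e*: fall in OPTION(5) among decliners, set to 0, 5 or 10 points

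**Overall arm difference** = (1 − q)·d − q·e

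| q | e = 0 | e = 5 | e = 10 |
|---|---|---|---|
| 10% | 9 | 8.5 | 8 |
| 20% | 8 | 7 | 6 |
| 40% | 6 | 4 | 2 |
| 50% | 5 | 2.5 | 0 |

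Example: q = 20%, e = 0 gives 0.8 × 10 − 0.2 × 0 = 8.

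The difference reaches zero at q = d / (d + e): 100% for e = 0, two thirds for e = 5, one half for e = 10.

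**What adjustment does.** A model with arm and preference as main effects has a single arm coefficient. When preference is balanced between arms, that coefficient is the same weighted average as above. Simulated data (400,000 patients, no clustering; assumed usual-care mean 40 in those wanting involvement and 35 in decliners, residual SD 15, d = e = 10) confirm it:

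| q | Unadjusted | Adjusted | With interaction: effect if wanting involvement | Interaction term |
|---|---|---|---|---|
| 20% | 6.01 | 6.01 | 10.02 | −20.00 |
| 40% | 2.06 | 2.01 | 10.10 | −20.17 |

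The effect in decliners is the sum of the last two columns: 10.02 − 20.00 = −9.98 and 10.10 − 20.17 = −10.07. Only the interaction model recovers the two effects that were built in. The adjusted estimate is no more informative than the unadjusted one about whether preference matters.

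**Stratum sizes.** Under Sampling, the aim is to recruit at least half of those identified: 90 / 2 = 45 per arm, spread over three practices. Six preference categories would average 45 / 6 = 7.5 patients per arm; three groups 15; two groups 22.5.

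**The case against.** - **The overall aim is directional.** The stated aim is to facilitate older patients' involvement, the Background describes a group that is too little involved, and Table 2 has messages promoting the benefits of shared decision-making. A higher-is-better score fits that aim. This stands, and it is why OPTION(5) should remain the putative primary outcome. Declining and matching are nevertheless designed functions of both components, and they go unmeasured.
- **The behaviour of OPTION(5) in decliners is not documented.** The items are not given, so a consultation in which the GP draws out and respects a wish for less involvement might score flat, lower or higher. This stands: a flat or falling score is an assumption.
- **A reader might infer that a respected decline counts as a failure.** The protocol does not support this. The score is continuous with no cut-off, no hypothesis test or p-value is planned, and the progression criteria concern recruitment, questionnaire response, consent and usable video, not OPTION(5) values.
- **Preference is already considered.** Interview patients are sampled partly by preference, Table 3 allows for an alternative measure, and satisfaction, trust and enablement might register a respected decline favourably. These help, but none measures agreement between wanted and experienced involvement. The detailed model may sit in an analysis plan, but the protocol names adjustment as the means of answering an effect-modification question, and adjustment does not answer it.
- **The remedy is imperfect.** The tool is mailed before the consultation. Recruitment procedures has the preference questionnaire handed out on arrival, while Table 4 calls it postal. Stated preference in the intervention arm may already be changed by the tool. This stands as a caveat.

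**Conclusion.** The point holds in a limited form. The intervention supports both seeking and declining involvement, the involvement measures run in one direction, and no listed outcome measures agreement with preference. The overall arm difference may therefore be diluted. With an assumed 10-point gain and no change in decliners it falls to between 9 and 5 points as decliners rise from 10% to 50%, and further if decliners' scores fall. These figures show the mechanism; they do not estimate its size in this trial.

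A reader might also infer that gains and losses would cancel and make a working intervention look inert. That needs a substantial fall in decliners together with a large share of them, such as a symmetric fall and 50%; nothing in the protocol establishes either.

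The part that needs no assumption about preferences or scores is the analysis: adjustment for preference yields one common effect and cannot show whether preference influences it. The consequence falls mainly on the judgement about outcome measures for the definitive trial.

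**What to change.** 1. Keep OPTION(5) as the putative primary outcome.
2. Under Preliminary evaluation of participant responses to the intervention, replace or supplement the adjustment with an arm-by-preference interaction estimate in the same hierarchical model, with a 95% CI and no p-value.
3. Tabulate mean and SD of OPTION(5) and collaboRATE by arm within two or three collapsed preference groups, defined in advance, not six.
4. Repeat the preference item on the post-consultation patient questionnaire, reworded as involvement experienced. Add to Table 4, as an additional descriptive outcome, the share of patients whose experienced involvement matched their stated preference, by arm with 95% CI.
5. Under Evaluation of outcome measures, use these results alongside the overall OPTION(5) mean when judging sensitivity.
6. Settle whether the pre-consultation questionnaire is postal or handed out on arrival, and report that preference in the intervention arm may have been recorded after the tool was received.

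The cost is one extra questionnaire item, one extra table and one extra model term. Strata will be small and clustered, so intervals will be wide and the results should be read as descriptive only.

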### Analysis

#### Recruitment capability, consent and randomisation procedures, sample characteristics

The trial will determine whether it is possible to recruit appropriate study participants to test the intervention, or whether amendments are required ahead of a future trial. The flow of participants will be summarised in a Consort diagram. Numbers of eligible clusters, individual participants identified and randomised, recruitment rates and attrition will be recorded.

The search strategy used to identify potentially eligible patients will be tested on different practice databases with a view to finalising a generic, universal search algorithm. Anonymised data on ineligible patients will provide a profile of those frequently excluded. Consideration will be given to whether adaptations to the trial could be appropriate, to enable these patients to participate in a future study.

Any difficulties with meeting recruitment targets (6 practices; at least 2 GPs per practice; at least 5 patients per GP) will be documented. Field notes and correspondence with practices will enable the issues to be explored. Patients’ reasons for declining will be reviewed in light of recruitment procedures. For example, patients will use the pre-consultation questionnaire to indicate whether they received the information pack in the post. The extent to which over-recruitment is necessary will be reviewed, as will the importance of incentivising participants.

Randomisation procedures will be discussed at team meetings to inform amendments prior to a larger trial. For example, consideration will be given to randomising more practices to the intervention than to usual care, to gather more data regarding intervention implementation if required. Consideration will be given to initiating the study in each of the three sites sequentially (e.g. inner city, then urban, then rural) in order to increase trial management capacity. Consideration will be given to blinding the research team for data analysis in the future trial.

Rates of patient consent, to the use of questionnaire data, to video-recording ([12]; Asan and Montague 2014) and to case note review, will be evaluated. Numbers lost to follow-up will be reviewed; however, it is anticipated that this will be minimal. The study will determine whether there are differential drop-out or recruitment rates between intervention and control groups (indicative of selection bias).

The degree of sociodemographic diversity in the sample will be reported in respect of generalisability of results. The external validity of the sample will be reviewed by comparing to relevant external datasets when reporting recruitment, selection procedures and participation rates (Steckler and McLeroy 2007).

#### Evaluation of data collection

Table 3 outlines the feasibility measures to be assessed regarding the collection of outcome data.

**Table 3 Tab3:** Evaluation of data collection procedures

Type of data collection (patient-, GP- or researcher-facing)	Components to be reviewed	Methods of analysis	Potential resultant amendments ahead of a definitive, larger trial
Patient-facing (questionnaires)		All patient-facing data collection forms have been reviewed for their suitability by Patient and Public Involvement (PPI) group	PPI members advised on the wording and format of questionnaires. PPI will provide a lay perspective on interpretation of feasibility findings.
	The feasibility of distribution and collection of patient questionnaires by receptionists.	Researcher’s field notes and follow-up correspondence with practices. Process evaluation interviews with patients.	Consideration of distribution by another means e.g. in the post (or email) prior to consultation.
	The appropriateness of collecting demographic data by patient self-report on pre-consultation questionnaires, as opposed to through the medical record.	Review of completeness of relevant items on patient questionnaires. Process evaluation interviews to discuss potential reasons for missing data. Correspondence with practices regarding practicalities of accessing patient demographic data with consent.	Consideration of accessing patient baseline data through practice records.
	Whether patient participants require assistance, encouragement or supervision to complete either of the questionnaires.	Researcher’s field notes and process evaluation interviews.	The provision of assistance to patients when completing questionnaires, e.g. providing staff to assist them or allowing more time pre- or post-consultation to allow the patient to seek help from a third party.
	Issues regarding time taken for questionnaire completion, any difficulties with comprehension of questionnaire items, numbers of questionnaires returned and reasons for missing data	Relevant quantitative data will be reported descriptively. Issues will be explored qualitatively with patients during process evaluation.	Time taken for completion may inform decisions surrounding when and how to distribute questionnaires. Issues regarding comprehension of specific items may lead to rewording with the assistance of the PPI group.
GP-facing (questionnaires and patient consent forms)	Issues regarding time taken for consenting patients, any difficulties with comprehension of items and reasons for missing data	Relevant quantitative data will be reported descriptively. Issues will be explored qualitatively with GPs during process evaluation.	Amendments to wording of consent form. Re-costing of incentive payments to practices if necessary, for extra consultation time to allow for consent.
	Issues regarding operation of video-camera to record consultation	Rates of incomplete, unusable or missing recordings will be reported. Issues will be explored qualitatively with GPs during process evaluation, through the researcher’s field notes and through correspondence with practices regarding any setup difficulties.	Review of existing technology and equipment provided, consideration of the need for prompts for GPs to initiate videos
	Issues regarding time taken for questionnaire completion, any difficulties with comprehension of questionnaire items, numbers of questionnaires returned and reasons for missing data	Relevant quantitative data will be reported descriptively. Issues will be explored qualitatively with GPs during process evaluation.	Issues regarding comprehension of specific items may lead to rewording. Re-costing of incentive payments to practices if necessary, for extra consultation time to allow for completion.
Researcher-facing (score sheets and templates)	The ability of members of the research team, to complete OPTION(5) score sheets based on review of video-recorded consultations.	Inter-rater reliability of OPTION(5) scores will be evaluated by calculating the inter-class correlation coefficient on ratings of all videos, aiming for values above 0.75. Comparisons will be made with other studies. The completeness and usability of video-recordings will also be reviewed as described above.	Review of training procedures for OPTION(5) measure if correlation low. Review of appropriateness of the measure in the context of this study if training appears sufficient. Consideration of the need for development of an alternative measure to be piloted ahead of a definitive trial.
	The case note template will be assessed for usability.	Any difficulties with comprehension of items by the research team will be reviewed in team meetings. Any challenges when obtaining the information required on case note review forms, including accessing and interpreting the information from the patient’s medical record, will be reviewed at team meetings. Inter-rater reliability for items on the case note review form will be evaluated by calculating an ICC on 20% of the data.	Re-wording and re-formatting of the template. Review of the qualifications required by the research team e.g. clinical academics only and level of qualification if so. Consideration of time frame for data collection, e.g. is 28 days sufficient to allow the notes to ‘settle’ and to capture all relevant documentation.

The study will assess the appropriateness of data collection procedures for use in the intended participant population as well as for the purposes of evaluating the intervention. Field notes from the research team, process evaluation interviews with participants and research meeting notes will guide an assessment of the appropriateness of measures. Participants’ ability to complete each patient-facing or GP-facing measure will be reviewed.

Assessments of the volume of data collection will establish whether it is appropriate to scale-up in a larger trial. This will include the time taken for field visits, data input and independent checking of the trial database. Overall completeness of data will be established, along with the impact of this on the potential usability of data to evaluate the effectiveness of the intervention.

